**5.2 Relationship to study product**

This can be classified as:

**None** adverse events felt to be due to extraneous causes that neither follow a known pattern of response nor a reasonable temporal relationship to study product

**Remotely related** adverse events that are unlikely to be related to product but which follow a reasonable temporal relationship, such that this cannot be completely excluded or events that could be associated with product but which are unrelated in time

**Possibly related** adverse events that may be due to extraneous causes but which follow a known pattern of response and/or a reasonable temporal relationship to study product

**Probably related** adverse events that cannot be explained by extraneous causes; which follow a know pattern of response and/or a reasonable temporal relationship; which disappear or decrease on cessation of study product and reappear on re-challenge

**5.3 Reporting adverse events**

Adverse events should be recorded on the appropriate case record form as to the nature of the event, the time it started and ended, the severity, probable relationship to the drug and any medication taken.

Grade 2 events probably or possible related to the vaccine should be discussed in the weekly Trial Management Group meetings.

Any grade 3 or 4 adverse event remotely, possibly or probably related to the immunization should immediately be reported to the PI or his deputy, who will fill in the appropriate forms and decide discontinuation of the vaccination schedule. The PI should if indicated arrange for urgent review of the case by the Steering Committee and report this to the monitor and the DSMC within 2 working days. The monitor will confirm that the event is potentially reportable and inform the Sponsor. Should the case be considered reportable by the DSMC, a report will be prepared by the clinical investigator or his deputy and filed with the Sponsor, Medical Products Agency and the Regional Ethics Committee.

**SAEs** should be reported to the monitor and the DSMC the same working day that the Clinical Investigator becomes aware of the event. This can be done by telephone or fax. The minimum criteria required in reporting a SAE are the participant identifiers (trial number/ date of birth/initials), reporting source (name of Investigator), and why the adverse event is identifiable as serious.

**The adverse event reporting:**

**telephone/[contact],**

**[contact]**

The PI arranges for urgent review of the case by the Steering Committee within 2 working days. The monitor will confirm that the event is potentially reportable and inform the sponsor.

Should the case be considered reportable by the DSMC, a report will be prepared by the clinical investigator or his deputy and filed with the Sponsor, Medical Products Agency and Regional Ethics Committee.

Examples of SAEs that do not require expedited reporting include:

- Hospitalisation for scheduled surgery unrelated to vaccine, other than temporally (within 30 days)
- Orthopaedic or traumatic injuries requiring hospitalisation
- Hospitalisation planned for pre-existing conditions not due to an aggravation in the condition
- SAEs occurring more than 30 days after vaccination or having appeared before vaccination without any aggravation after vaccination

**5.4 Clinical management**

Events will be managed by the clinical trial team who will assess and treat the event as appropriate.

**6 Management of HIV issues during and following the trial**

Individuals who test HIV-positive during the screening process will be offered care according to Swedish national guidelines at Venhälsan or referred to a care giver of their choice.

**6.1 HIV testing**

Only volunteers with a negative HIV antibody/antigen test result will be enrolled. A risk assessment will be undertaken prior to every immunisation and if risk status has changed then immunisation may have to be delayed until the HIV status of the participant is clarified. It is possible that participants may develop antibodies and test ‘positive’ in routine HIV ELISA assays subsequent to immunisation. The immunological and virological laboratories at SMI, will conduct additional tests to distinguish between infection and a post-immunisation response required either for clinical management, or at the request of a participant. The results from these tests will only be known to the study staff as positive or negative for HIV infection. At the end of the study specimens will be tested in real-time so that participants can be informed of the result and a plan to recall and retest them made should this be necessary. In the event of ongoing post-immunisation positive ELISA, the participants will be invited to re-attend annually until such time as this response has disappeared, and provided with an explanatory identity card in the interim.

*6.1.2 Verification of HIV status of participants*

If certification is required at the request of the participant, this can be provided by the trial team after testing at the local laboratory.

Results will always be given at an interview with a member of the study team unless the participant requests an independent physician, in which case this will be arranged.

If a specimen from a participant suggests that the participant is HIV infected, a second specimen will be collected and retested.

If a subject for any reason needs to establish his or her HIV status extended tests will be offered i.e. HIV RNA PCR or antigen test.

**6.2 HIV infection**

In the unexpected circumstances that a participant in the trial acquires HIV infection, they will be managed in the following way:

*6.2.1 Referral for clinical care*

Participants will be referred initially to a specialist physician at Venhälsan for a full discussion of the clinical aspects of HIV infection and planning for further care. Further investigations will be undertaken as necessary.

*6.2.2 Referral for counselling:*

A referral to a counsellor at Venhälsan will be arranged by the specialist physician. The counselling process will assist the participant in the following issues:

1. psychological and social implications of HIV infection
2. who to inform and what to say
3. implications for sexual partners
4. avoidance of risk to others in future

*6.2.3 Informing the other involved health care personnel and dentist*

The participant will be encouraged to do this, but the decision will remain at the discretion of the individual.

*6.2.4 Immunological follow-up*

Follow-up of HIV infected individuals who have received study vaccine products will be determined by the Trial Management Group. The intensity of assessments will be dependent both on the number of immunisations received by the individual and their clinical progress, including changes in disease markers such as viral load and CD4 count.

If a volunteer is found to be HIV-infected during the trial, he/she will be excluded from further immunizations in the trial.

**6.3 Social discrimination as a result of a post-vaccine response**

The aim is to minimise the possibility of social discrimination in participants who develop a positive HIV-ELISA test by providing HIV testing by PCR and certification for participants as required. In addition, an identification card stating that the individual has participated in a vaccine trial, with a contact number in case of medical emergency, will be provided.

In the unlikely event that a participant suffers social discrimination as a result of a post-vaccination response, the clinical investigators will assist the participant.

**7 Management of the trial**

**7.1 Data management at the Clinical Centre**

All procedures will be performed according to GCP. Data will be recorded directly onto the case report forms, which will provide the bulk of the data for the trial. The volunteer will only be identified by the study number and initials in the CRF. There will be additional confirmatory and source data in the clinical notes, such as medical history related to eligibility, results of laboratory analyses, dates of visits including immunisation, and details of clinical management (description of adverse events and concomitant medication). One photocopy of the completed case report form will be forwarded to the trial coordination centre for inspection and entry into the database.

Any changes to the CRFs should be done without obscuring the original entry, signed and dated, including changes made before a copy is forwarded to the trial coordination centre for inspection and data entry.

Study related documents should be kept in a secure location at least 15 years after completion of the trial. Clinical notes and original laboratory results should be kept according to applicable laws.

**7.2 Data management in the virology/immunology laboratories**

Standardised operating procedures according to GCLP will be followed in all laboratories to ensure the quality of the data. Data will be stored electronically in an agreed format and data files transferred to the trial coordinating centre for the main analysis.

**7.3 Data management at the trial coordination centre**

All CRFs will be reviewed for completeness and inconsistencies by the data manager according to standardised operating procedures. Any enquires will be communicated with the clinical centre and will be passed for review by the trial physician if required. The data manager will approve the CRFs for data entry into the data base. Data will be coded and entered into a computerised database. Consistency checks and range checks will be performed at the data entry level.

The patient database Melior will be used under the same security arrangements as for patient records.

After approval and entry into the database, the copy including documentation detailing all the queries and changes will be stored in a study specific binder at the trial coordination centre. The documents in the binder will be organised due to study number. The original case report forms will be stored together with the individual source data at the clinical centre.

**7.4 Monitoring**

The monitor will be recruited from Karolinska Trial Alliance, a Swedish study-independent centre with GCP educated professional staff specialized in study-associated services.

Karolinska Trial Alliance (KTA) [name], [name]

http://www.karolinskatrialalliance.se/

The monitor will be responsible for:

- Monitoring the trial according to ICH GCP guidelines including monitoring vaccine accountability, and dispatch and arrival of virological and immunological specimens
- Preparation of reports to assist the monitoring

The monitor will visit the clinical center to validate trial data against the clinical records. The monitoring will adhere to ICH Good Clinical Practice guidelines. The following data should be verifiable from source documents:

- completeness of the study file including all approvals, CVs etc
- documentation of any existing conditions or past conditions relevant to eligibility
- signed consent
- dates of visits including dates of immunisations
- source verification of all laboratory data which are out of the normal range entered into the data base
- source verification of all grade 2 or above adverse events entered into the data base

and any events leading to discontinuation of the immunisation schedule

Vaccine returns will also be monitored at visits to the clinical centre/pharmacy*.*

**7.5 Data Ownership**

The data generated in this study will be the property of SMI and made available to the Steering Committee for analysis and publication. If required at an earlier date for the purposes of regulatory submissions, a request should be made to the Trial Coordinating Committee.

- 1. **Trial committees**

*7.6.1 Steering Committee (SC)*

The supervision of the trial will be a responsibility of the Steering Committee (SC). It will also be charged with the compilation of data, analysis and final reports from the study. The committee will have an independent chair, [name]. The members will include [name], [name], [name], Associated professor [name], [name] and [name] or their deputies.

Additional non-voting members will attend as appropriate to the contents of the meeting. This committee will be responsible for final decisions about grade of adverse events and relationship to study vaccine. The Steering Committee may form an endpoint committee to review the grade of adverse events and relationship to study vaccine, and the independent members will have an additional casting vote should this be required. Notes of meetings will be kept.

The trial may be terminated by this Committee for any reason, including on the recommendation of the DSMC.

*7.6.2 Trial Management Group (TMG)*

This group will oversee the day to day running of the trial and the members will be primarily related to the clinical and data management teams. The immunologists will join if there are relevant items on the agenda. Notes will be taken and will form the basis of the progress report to the Trial Coordinating Committee.

- 1. **Data and Safety Monitoring Committee (DSMC)**

An independent Data and Safety Monitoring Committee (DSMC) will be established by the sponsor to assess at intervals the progress of the clinical trial, the safety data, and the endpoints, and to recommend to the sponsor whether to continue, modify, or stop a trial. In the case of voting, the chairman will have the final say. The DSMC will meet in order to review the safety data after half of the participants have completed the full immunization regimen. Written reports of their meetings will be submitted to the Sponsor and the SC. The members of this DSMC are:

[name] Chair

[name] Clinician

[name] Clinician

*7.7.1 Indications for additional reviews*

There will be an additional meeting if any of the participants experience any grade 3 or 4 clinical or laboratory event (confirmed on attendance or repeat testing) not resolved within 72 hours and considered probably or possible and likely to be related to vaccine product or any reportable SAE. The DSMC will also be consulted in case of any event that is unexplained or unexpected that could pose a possible threat to the safety of the participants, SUSAR. The DSMC may also meet and ask for safety or efficacy data at their own discretion for any reason of their own.

*7.7.2 Interim analysis*

An interim analysis will be performed for safety when 10 volunteers have received the first electroporation and when half of the volunteers have received the last DNA injection.

*7.7.3 Indications for discontinuation of immunisations in all participants*

See section *3.7.2* above

*7.7.4 Analysis*

An analysis plan will be submitted to the DSMC before the code is broken.

### 8 Statistical considerations

**8.1 Sample size**

Safety: By the end of this study an additional (compared to previous clinical trials) 40 participants will have been exposed to HIV DNA and 30 the HIV MVA. In addition 36 individuals will have been exposed to 3 electroporation procedures and will be described in the qualitative safety evaluation. This is considered sufficient for the planning of continued studies.

Immunology, secondary endpoints: The size of the groups (10+2) and the comparisons described below, 8.2, is judged to be sufficient in a descriptive study in order to formulate the hypothesis to be tested in a planned trial in Tanzania.

**8.2 Analysis**

All safety end-points will be graded by the Clinical Investigator and reviewed by the Trial Management Group. Any queries about grade and relationship to study product that cannot be resolved will be referred to the Trial Coordinating Committee for a final decision.

The primary end-points:

1. The safety of immunization with the seven or eleven DNA plasmids carrying HIV-1 genes will be assessed by clinical signs and standard biochemical and haematological laboratory tests where any worsening of the severity grade will be considered for causality with the vaccine.
2. The immunization will be evaluated by assessing local (pain, cutaneous reactions including induration), general (fever, chills, headache, nausea, vomiting, malaise, myalgia) and other unsolicited adverse events within 7 and 28 days. Any grade 3 or 4 event will be taken as an indication that the arm is less tolerable.

The secondary endpoints

The secondary endpoint (immunogenicity) will primarily be assessed by IFN-γ ELISpot 2 weeks after the third DNA immunization, the fourth DNA or first MVA immunization and after the fifth DNA or second MVA immunization. Both number of responders and magnitude of responses will be tested for significance. Additional studies will be performed at other time points using other assays such as intracellular cytokine staining, lymphoproliferation assays, epitope mapping, binding (and if indicated) neutralization antibody assays.

Group B1 will be compared with the id only group in the HIVIS study (Group A in HIVIS trial) for evaluation of the lower dose of HIV DNA (0.6 vs 1.0 mg).

Group B2 will be compared with Group B1 for evaluation of the lower dose of HIV DNA with and without electroporation.

Group B3 will be compared to the group B2 for the evaluation of HIV DNA as a boost compared to boosting with HIV MVA.

Group B4 is will be compared to groups B1-B3 to show if priming with additional HIV-related plasmids will increase immunogenicity to any of the included antigens.

Figures/tables will be prepared including all participants’ results.

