A phase I trial (HIVIS 01/02) with a multi-subtype HIV-1 DNA vaccine boosted with a vaccinia vector (MVA) with the corresponding HIV-genes inserted into it, has been successfully conducted in our clinic in Sweden. The combination of DNA and MVA was proven safe and highly immunogenic as 34/37 (92%) of participants reached the primary endpoint of positive IFN gamma ELISPOT of whom 31 reacted to gag peptides and 24 to env peptide pools. Including also other assays of HIV-specific immune responses, 97% (all but one subject) of the cohort participants, developed HIV-specific immune responses. All DNA injections were given by the Biojector2000 needle-free device. Preliminary analysis indicates that ¼ the dose DNA given id primes an immune response equally as well as a ‘standard’ 4 mg dose given im, and that boosting with MVA could be achieved in the presence of vaccinia immunity. Volunteers above 40 years of age mounted a significantly lower immune response to the immunogens. It was also evident that the higher dose of MVA (108 pfu) delivered im gave better boosting of the DNA primed responses than when 107 pfu of MVA was given id. However, in order to administer the DNA intradermally, five shots with the Biojector were required at each immunisation time point. In contrast to the prominent T cell responses detected after immunization only weak anti-HIV antibody responses were observed (Sandström et al., 2008).

A further placebo-controlled phase II trial (HIVIS 03) in Dar es Salaam (MUHAS) of 60 non-infected individuals has confirmed the safety and immunogenicity of the HIVIS DNA and HIV MVA boost schedule. The study is now unblinded and analysis presented at the AIDS vaccine meeting in Paris 2009 (Bakari, et al., 2009). Since 1986 laboratory and clinical capacity building has taken place in Dar es Salaam, Tanzania, through the SIDA/Sarec TANSWED programme. This has led to the introduction of HIV vaccine studies in line with the Tanzanian National HIV Vaccine Strategic framework under the European Community program HIVIS, supported by both SIDA/Sarec and EU. An extension of this trial, TaMoVac has been funded by EDCTP. It is also anticipated that a further trial will be needed to introduce the technique for administration of vaccines (electroporation). This has passed through all the application steps for funding from EDCTP.

*HIV vaccine strategies under investigation*

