**General plan**

**1.1 Objectives**

Primary

Is it safe and tolerable to immunize with seven or eleven DNA plasmids carrying HIV-1 genes with electroporation?

Secondary

1. Is it possible to increase immunogenicity of a DNA vaccine delivered intradermally and to reduce the number of injections needed by using electroporation?
2. Will electroporation improve/alter the quality of the immune responses induced by the HIV-1 DNA plasmids?
3. Is it possible to obtain similar immune reactivity by replacing two intramuscular boosts using MVA with two intradermal injections of HIV-1 DNA plasmids together with electroporation?
4. Can electroporation increase immunogenitcity of all included DNA plasmids to permit mixing of all vaccine plasmids instead of delivering them as two different entities?
5. Will additional DNA plasmids broaden the immune response?

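### Secondary objective 3 asks whether the DNA + electroporation boost is similar to MVA, but section 8.2 offers only significance tests at 10 v 10, which cannot show similarity

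*Protocol*

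**What the plan says.** Secondary objective 3 (Protocol, Synopsis and section 1.1) is a similarity question: "Is it possible to obtain similar immune reactivity by replacing two intramuscular boosts using MVA" with intradermal DNA given with electroporation. Section 8.2 assigns it to one pair of groups: "Group B3 will be compared to the group B2 for the evaluation of HIV DNA as a boost compared to boosting with HIV MVA".

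Section 8.2 makes IFN-γ ELISpot two weeks after each of the third, fourth and fifth immunisations the main immunogenicity assessment. It then says of all the immunogenicity comparisons: "Both number of responders and magnitude of responses will be tested for significance". It also promises figures or tables with every participant's results. No definition of similar is given.

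Section 8.1 gives no power or effect size for these comparisons. It states: "The size of the groups (10+2) and the comparisons described below, 8.2, is judged to be sufficient in a descriptive study", with the purpose "in order to formulate the hypothesis to be tested in a planned trial in Tanzania". Section 7.7.4 announces an analysis plan before the code is broken. That plan is not shown.

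**The concern.** The question and the method point in opposite directions. A significance test asks whether the data are incompatible with no difference. If it does not reject, that says nothing about similarity unless the interval around the estimate also excludes a loss that matters. With ten vaccinees per arm that interval is wide whatever is observed.

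Objective 3 asks whether one boost can replace another, and its answer is meant to shape the hypothesis for the planned trial in Tanzania. If the report can offer only a p value for B3 v B2, a non-significant result leaves the objective unanswered and is easily misread. This is more than detail left to an analysis plan, because section 8.2 itself fixes a difference test for a similarity question.

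**Working it through.** **The plan's own figures.** Section 8.1 gives only exposure counts, and the design table reproduces them: 4 × 10 = 40 exposed to HIV DNA; 3 × 10 = 30 to MVA (B1, B2, B4); 3 × 12 = 36 to electroporation (B2, B3, B4, placebo included). There is no stated power to reproduce.

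**Inputs.**
- Vaccinees per arm: 10 v 10 (design table). Late drop-outs are not replaced (section 2.4), so this is a best case.
- Responder rate after MVA, assumed for B2: 34/37 = 0.919, from the Introduction ("34/37 (92%) of participants reached the primary endpoint of positive IFN gamma ELISPOT"). A rate of 0.80 is used as an alternative.
- Assumed, because the protocol does not state them: two-sided 0.05, Fisher's exact test for responders, Mann-Whitney or t test for magnitude.

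**Responders, Fisher, exact enumeration.** P(significant) = Σ P(B2 = a) · P(B3 = b) over all pairs (a, b) with p < 0.05. Where B2 is higher, significance needs b ≤ 5 if a = 10, b ≤ 3 if a = 9, and b ≤ 2 if a = 8. For true rates 0.919 and 0.60 the main terms are:

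- a = 10: 0.4293 × 0.3669 = 0.1575
- a = 9: 0.3788 × 0.0548 = 0.0208
- a = 8: 0.1504 × 0.0123 = 0.0018

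The sum is 0.180, so 82% of trials are non-significant. Other scenarios:

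| B2 | B3 | Non-significant (Fisher) |
|---|---|---|
| 92% | 70% | 93% |
| 92% | 60% | 82% |
| 92% | 50% | 66% |
| 92% | 40% | 47% |
| 92% | 30% | 28% |
| 80% | 50% | 87% |
| 80% | 40% | 75% |

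An uncorrected chi-square or Barnard test is less conservative: 66% non-significant at 92% v 60%, and 47% at 92% v 50%. Single results by Fisher: 10/10 v 6/10 gives p = 0.087; 9/10 v 5/10 gives p = 0.14; 9/10 v 4/10 gives p = 0.057.

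**Magnitude as well.** Section 8.2 also tests magnitude, so the Fisher figures alone overstate the problem. Suppose each response is normal with SD 1 and a responder is anyone above a fixed threshold. Then 92% v 60% is a shift of 1.398 - 0.253 = 1.14 SD. Simulating Fisher and Mann-Whitney together, neither is significant in about:

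- 37% of trials at 92% v 60%
- 19% at 92% v 50%
- 60% at 92% v 70% (0.87 SD) or 80% v 50% (0.84 SD)

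A t test at 10 v 10 has 40% power at 0.8 SD, 56% at 1.0 SD and 80% at 1.33 SD.

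**Precision when the arms agree.** The Wilson limits for 9/10 are 0.596 and 0.982. The Newcombe half-width for 9/10 v 9/10 is √[(0.900 - 0.596)² + (0.982 - 0.900)²] = 0.315, so the 95% interval is about -32 to +32 points. For 10/10 v 10/10 it is -28 to +28.

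**Would a margin help?** For non-inferiority on responders with both true rates p = 34/37, one-sided 0.025 and 80% power, n per arm = (1.96 + 0.84)² × 2p(1 - p) / margin². This gives 117 for 10 points, 52 for 15, 30 for 20 and 13 for 30. Ten per arm is too few for any of these.

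**The case against.** The strongest reply is that the protocol never claims what a critic might fear. Immunogenicity is secondary and section 8.1 limits its purpose to forming a hypothesis. The sentence on significance is generic to all the immunogenicity comparisons, and individual results will be displayed. An analysis plan is still to come. Most of this stands, and it rules out four stronger readings:

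- A reader might infer that a non-significant B3 v B2 result will be declared similar. No such decision rule is written.
- A reader might infer that the MVA boost would then be dropped in the follow-on trial. The Introduction keeps MVA among the options there, and nothing ties that choice to this p value.
- A reader might see a contradiction between a descriptive study in 8.1 and significance tests in 8.2. Nominal, unpowered tests are compatible with a descriptive study.
- A reader might conclude from the 82% that a large loss would usually be missed. That figure is for responders alone by Fisher. With magnitude tested too, the same loss is missed in about 37%, and larger losses less often.

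The reply does not remove the mismatch. The descriptive aim is an argument for estimates with intervals, and displaying individual values does not say how far apart the two boosts could be. An analysis plan that follows 8.2 as written would inherit the problem.

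**Conclusion.** The point holds in a limited form. The only inferential method that section 8.2 gives for B3 v B2 cannot answer objective 3, and the protocol supplies no other. With 10 v 10, moderate losses (92% v 70%, 80% v 50%) escape both tests in about 60% of trials and 92% v 60% in about 37%. Identical results still leave roughly ±30 points of uncertainty in responder rate.

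These figures assume that 34/37 carries over to B2, two-sided tests at 0.05, Fisher for responders and, for the joint figures, a latent-normal response. The principle depends on none of these: non-significance at this size is not evidence of similarity. Because immunogenicity is secondary and hypothesis-forming, this is a worthwhile correction to the analysis section and not a flaw in the design.

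**What to change.** In section 8.2, for B3 v B2 at weeks 38 and 62:

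- Make the main result the difference in responder proportions with its 95% confidence interval. Also give the ratio of geometric mean ELISpot responses with its 95% confidence interval, adjusted for the week-36 pre-boost value. B2 and B3 are treated alike up to that sample, and it is already scheduled in section 2.6.
- Name the interval method. At this size interval and test can disagree: 10/10 v 6/10 gives Fisher p = 0.087 but a Newcombe interval of 4 to 69 points.
- State that a non-significant test is not evidence of similarity, and that at 10 v 10 the result serves only to form the hypothesis, in line with 8.1.

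A formal similarity margin adds little at this group size and is not needed. The cost is wording in the protocol and the analysis plan, with no new participants or samples. The downside is that the likely answer to objective 3 becomes that similarity was not shown.
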